## Abstract

**Background:** Sports-related concussion (SRC) is a complex injury with heterogeneous presentation and management. There are few studies that provide guidance on the most effective and feasible strategies for recovery and return to sports participation. Furthermore, there have been no randomized studies of the feasibility, safety, and efficacy of early rehabilitation strategies across multiple sports and age groups. This international cluster-randomized pragmatic trial evaluates the effectiveness of early multi-dimensional rehabilitation integrated with the current return to sport strategy vs. the current return to sport strategy alone.

**Methods:** The study is a cluster-randomized pragmatic trial enrolling male and female athletes from 28 sites. The sites span three countries, and include multiple sports, levels of play (high school, college, and professional), and levels of contact. The two study arms are Enhanced Graded Exertion (EGE) and Multidimensional Rehabilitation (MDR). The EGE arm follows the current return to sport strategy and the MDR arm integrates early, MDR strategies in the context of the current return to sport strategy. Each arm employs a post-injury protocol that applies to all athletes from that site in the event they sustain a concussion during their study enrollment. Participants are enrolled at pre-season baseline. Assessment timepoints include pre-season baseline, time of injury (concussion), 24–48 h post-injury, asymptomatic, and 1-month post-injury. Symptoms and activity levels are tracked post injury through the return to play process and beyond. Injury and recovery characteristics are obtained for all participants. Primary endpoints include time to medical clearance for full return to sport and time to become asymptomatic. Secondary endpoints include symptom, neurocognitive, mental status, balance, convergence insufficiency, psychological distress, and quality of life trajectories post-injury.

**Discussion:** Outputs from the trial are expected to inform both research and clinical practice in post-concussion rehabilitation across all levels of sport and extend beyond civilian medicine to care for military personnel.

**Ethics and Dissemination:** The study is approved by the data coordinating center Institutional Review Board and registered at clinicaltrials.gov. Dissemination will include peer-reviewed publications, presentation to patients and public groups, as well as dissemination in other healthcare and public venues of interest.

## Introduction

Concussion is a complex injury. Athletes who sustain a sports-related concussion (SRC) present with a diverse array of symptoms and recovery trajectories (1). Unfortunately, there is limited empirical evidence for clinicians to use in selecting the most effective and feasible strategy for recovery, rehabilitation, and return to sport. Currently, return to activity recommendations are based on expert consensus, with relatively few randomized controlled studies directly evaluating return to sport strategies (2). There are few clinically directed and pragmatic options to guide clinicians responsible for implementing concussion treatment/rehabilitation, particularly during the early acute/sub-acute presentation phase. A conservative strategy of restrictive physical and cognitive rest (i.e., removing athletes from participation and placing him/her on rest until normal brain functioning returns), was long considered to be the preferred therapeutic option for athletes post-concussion and was endorsed as the standard of practice by expert panels (3). This strategy is often frustrating for athletes, given they tend to be physically-focused, task-orientated individuals. In fact, recent evidence suggests that strict, total rest may actually prolong functional recovery following concussion (4). Over the past 5 years the evidence base concerning active management and rehabilitation strategies for concussion has significantly grown and suggests various interventions may be beneficial, especially in athletes with prolonged symptoms (5–7) However, it remains unclear to what extent these active strategies can be employed without negatively affecting recovery (e.g., exacerbating symptoms, prolong symptom recovery, etc.). There is scientific and clinical concern that prematurely implementing overly-aggressive activities has the potential to worsen symptoms and delay return to activity in athletes (8, 9).

There are limited data promoting a systematic approach to early rehabilitation and post-concussion activity that is modifiable throughout the return to sport process based on symptom presentation and sport specific requirements. Young adults with cervicogenic and vestibular symptoms experiencing prolonged concussion symptoms demonstrated improved outcomes and accelerated recovery when engaged in targeted therapy to address these dysfunctions (10–12). Aerobic exercise within a symptom limited heart rate range also improves recovery and outcomes in individuals with prolonged symptoms (6, 13). However, such interventions may not consider other areas such as balance or visual disturbance and have not been fully evaluated in the context of the current return to sport paradigm in a pragmatic field setting. While some of these studies were published after the current trial protocol development, they serve as evidence for the need to further evaluate various intervention methods post-concussion, even today.

To date, no studies have addressed key and focused strategies that can be feasibly implemented at a low cost and with few resources early in the treatment process. Furthermore, no studies have prospectively evaluated the current return to sport strategy and direct integration of early, multifaceted activities into this paradigm. Additionally, no studies to date have developed a comprehensive strategy for providers to begin engaging athletes with clinically directed and symptom-based activities immediately following the recommended (14) 24–48 h rest period. Such studies are needed for application across a wide variety of sports medicine and clinical settings. In order to develop best practices for the safe and effective use of these new therapies, there is a need for **pragmatic field trials** to support the accurate development of guidance for the use of early, active rehabilitation therapies, relative to current practice.

To address this gap, we are conducting a pragmatic cluster-randomized trial with two parallel groups. Of note, the trial was designed in 2016 and the outcomes and interventions selected were based on the following factors most relevant and applicable at that time: (1) common data elements in large-scale concussion studies (15); (2) pragmatic assessments and exercises that would apply in a variety of settings and that do not require extensive resources; and (3) logical intersection with the current return to sport paradigm. The trial includes athletes of varying age and levels of skill, from multiple countries, from multiple sports, and across multiple care models to understand the influence of early activity in the context of the return to sport strategy on outcomes following sport-related concussion. The two Specific Aims for this trial are to: (1) evaluate the effectiveness of the enhanced graded exertion (EGE) progression (current return to sport strategy) vs. an early, activity rehabilitation [multidimensional rehabilitation (MDR)] strategy; and (2) evaluate the safety and feasibility of these protocols.

## Methods and Analysis

### Overview and Structure of the Active Rehab Study

The Active Rehab Study Consortium was initially proposed in 2014 through an international meeting that included representation from the scientific community and sporting organizations. The core idea of a multi-sport, multi-age, and multi-country study evaluating treatment and management of concussion was refined into a formal protocol over a period of months by an executive research consortium. They titled this project “Role of Active Rehabilitation in Concussion Management: A Randomized Controlled Trial (The Active Rehab Study).” The final consortium, led by The University of North Carolina at Chapel Hill and Medical College of Wisconsin, includes collaborators and sites from the Canadian Football League (CFL, 9 team sites), New Zealand Super Rugby (NZR, 5 team sites), North American Colleges/Universities (6 school sites), and Wisconsin and North Carolina High Schools (8 school sites). Sports represented in the study include collision, contact, and non-contact sports for both males and females. Should professional cohort sample size not approximate anticipated numbers, an additional professional ice-hockey cohort may be included. The study is conducted in compliance with US and international guidelines for research under the primary protocol approval from The University of North Carolina at Chapel Hill Institutional Review Board. All participants provide written and informed consent prior to participation. Informed consent documentation is verified via an informed consent tracking form in the study data collection system and through communication with study cohort leads and sites throughout the course of the study.

### Allocation to Study Arm

The two treatment arms (multidimensional active rehab and EGE progression) are assigned at random to the 28 sites in the study. Site level (cluster) randomization is utilized because the study team considered that patient-level randomization at a site would be prone to contamination between arms. Thus, all athletes at a given site receive the same protocol. All study sites are randomized to either the MDR (early rehabilitation) or the EGE [current return to sport strategy (16)]. To ensure a balanced of treatment arms across cohort, site randomization is stratified by (i.e., conducted within) cohort (NZR, CFL, College, HS). Colleges/universities and high school sites are stratified by size of school prior to randomization; CFL and NZR sites are not stratified. Due to the nature of the early and active treatment delineation, no allocation concealment such as masking or blinding is possible. The clinicians (site personnel) at the sites know their allocated arm. However, participants are not explicitly told about the role of their respective study arm. Site personnel at the MDR sites are trained to deliver the treatment separately from the site personnel at the EGE sites.

### Participants and Eligibility Criteria

The inclusion criteria for participants in the trial are individuals rostered as an athlete at the study sites who consent to the study. Written, informed consent is administered during a pre-season baseline assessment. Target participant enrollment across all settings is estimated to be 3,500 at baseline and 100–200 in each study arm (total *n* = 200–400) post-injury. The post-injury protocol includes all consented athletes with a SRC at each site and meeting the following criteria.

Our current trial aligns with common elements from the NCAA-DOD Grand Alliance Concussion Assessment, Research, and Education (CARE) Consortium (15). As such, we have defined SRC in accordance with the Department of Defense (DoD) operational definition as *a change in brain function following a force to the head, which may (or may not) be accompanied by temporary loss of consciousness (if LOC, temporary is defined as* <*30 min based on the Mayo TBI severity guidelines), but is identified in awake individuals with measures of neurologic and cognitive dysfunction, as indicated by 1 or more of the 22 symptoms from the Sport Concussion Assessment Tool (SCAT) symptom checklist* (16). No athlete with a Glasgow Coma Scale <13 enters the treatment progression of either arm.

As is standard with SRC studies (15), identifying the SRC is determined by medical professionals at each site involving a physician and other team-based healthcare provider (based on clinical exam and their interpretation of objective findings inclusive of the definition above). If medically diagnosed with a SRC, and no other indicators of more moderate to severe TBI as defined in the Mayo definition above (17), consented participants are eligible for enrollment in the treatment protocol. Documentation of the clinical diagnosis and identification of the medical personnel making the diagnosis are recorded in study case report forms. For inclusion in the post-injury protocols, the SRC must occur in a rostered sport for a high school or collegiate sport at their school or for their specific rostered sport (and team sanctioned activity) for the professional cohort. Individuals with any positive/abnormal clinical neuroimaging finding(s) following injury are not entered into the post-injury protocol or are discontinued from their arm treatment protocol if these findings are observed after the protocol has been initiated. Although these individuals are discontinued from the treatment protocol, we continue to collect assessment time point data on these individuals and documentation for their overall care.

We anticipate ~10–15% attrition due to study demands and seasonal nature of sport through full clearance to return to sport. However, we expect 20–30% attrition for the 1-month timepoint due to this timing and other potential participant follow-up issues. The study protocol incorporates contacting participants to keep them engaged.

### Study Arms and Treatment Protocols

The two study arms are EGE and MDR. The EGE arm primarily follows the current consensus return to sport progression (Table 1). The MDR arm includes early, active rehabilitation that is integrated into the EGE/return to sport progression. Overall, the difference between study arms is the inclusion of early, active rehabilitation (Figure 1).

**Table 1 T1:** 5th International Consensus Statement on concussion in sport return to sport strategy.

**Rehabilitation Stage**	**Functional exercise at each stage of rehabilitation**	**Objective of each stage**
**1. Symptom-limited activity**	Daily activities that do not provoke symptoms	Gradual reintroduction of work/school activities
**2. Light aerobic exercise**	Walking or stationary cycling at slow to medium pace. No resistance training	Increase HR
**3. Sport-specific exercise**	Skating drills in ice hockey, running drills in soccer. No head impact activities.	Add movement
**4. Non-contact training drills**	Progression to more complex training drills (e.g., passing drills in football and ice hockey). May start progressive resistance training	Exercise, coordination, and increased thinking
**5. Full contact practice**	Following medical clearance, participate in normal training activities	Restore confidence and assess functional skills by coaching staff
**6. Return to play**	Normal game play	

*From McCrory et al. (16) 5th International Consensus Statement on Concussion in Sport (NOTE: Our study was designed prior to the 2016 strategy being released, however, in anticipation of Stage 1 changing to limited/symptom guided activity, our design always included that as part of Stage 1 and the remainder of the strategy remained the same)*.

**Figure 1 F1:**
[figure not shown]
Key study activities by study arm.

Participants in both arms, and at all sites, are enrolled into the overall study at pre-season baseline. However, the site's treatment protocol is only activated following concussion injury. Specifically, the post-injury protocol for both arms is only activated if the consented athlete suffers a concussion related to their rostered sport of interest at a team sanctioned event and meet enrollment criteria post-injury.

Following activation of the protocol post-injury, all concussed participants are given guidance on recommended physical activities in which they can engage. This guidance is consistent with the 5th International Consensus Statement on Concussion in Sport (16). Of note, our study was designed prior to the 2016 strategy being released, however, in anticipation of Stage 1 changing to limited/symptom guided activity, our design always included this type of language as part of Stage 1, as well as more generic descriptions of each stage. Participants are also instructed by their site medical staff on how to be observant for increases in symptoms. This guidance—which focuses on guided activity rather than restriction—is provided via a hardcopy educational instruction sheet and a short video. These materials are provided to all participants following injury. All concussed participants also keep a daily physical and cognitive activity summary log from 24 to 48 h post-injury through 7 days post return to play. A small subset of participants wears activity tracking technology to track physical activity from time of injury to full return to play. There is no predetermined sample size for the activity trackers as this is an ancillary component only. The activity log information serves as the primary compliance measure, as well as measures of activity that may affect recovery (covariates). To enhance compliance for log completion, participants are sent email reminders where applicable and completion is monitored by site clinicians for all sites.

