Progression through the MDR protocol follows a standardized set of rules (Table 2). Progression from Phase I (Symptom Control) to Phase II (Perceived Impairment Reduction) requires that an individual's symptoms must not increase 10 or more points compared to their lowest symptom assessment since injury, and they must not have any symptoms with a symptom score of 5 or 6 at the beginning of a subsequent intervention session. When the participant completes activities in the phase where symptoms remain stable/do not increase beyond reliable change from beginning of one session to beginning of another (see “stable” above), the participant will be progressed to the next phase. We expect some increase from beginning to the end of a session, but we expect this to decrease by the start of the next session. Participants should on average, complete four sessions per week until fully returned to play. One session each week may be completed at home (i.e., unsupervised) as directed by a team healthcare provider. Each session lasts ~20 min and is conducted at the clinician's discretion. Once enrolled into the MDR study arm, each participant completes a minimum of two sessions in Phase I (Symptom Control). The MDR activities may commence prior to beginning the EGE progression and should be integrated with EGE activities once a participant is asymptomatic.

**Table 2 T2:** Multidimensional rehabilitation progression (Active Rehab).

**Rehabilitation stage**	**Notes**	**Goal**
**Entry into Phase I** (to the intervention progression)	*Symptoms not getting worse*. ∘ Symptom score not increasing by 10 or more over a 24 h/1 day period from their initial symptom assessment (6 h or 24–48 h assessment) ▪ Most people will be eligible at this time ▪ The earliest someone could start the intervention would be 24–48 h post-injury	Stabilization of symptoms
**Phase I**	*Must complete a minimum of **2 sessions** in this phase* Progression to Phase I may occur when: ∘ An individual's symptoms must **not** increase 10 or more points **compared to their lowest symptom score since the injury** ∘ They must not have any individual symptom items with a severity score of **5 or 6** when assessed at the beginning of a subsequent intervention session at Phase II (this would be the third session or beyond)	Symptom control and introduction to the intervention

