### Study Outcomes and Assessments

The primary trial endpoints include time to asymptomatic/symptom free and time to full clearance for return to sport, in days. The secondary endpoints include clinical and quality of life outcomes assessed from baseline through 1-month post return to play, as well as safety and feasibility outcomes. An assessment protocol similar to the NCAA-DOD Grand Alliance Concussion Assessment, Research, and Education (CARE) Consortium's is utilized for both baseline measurements and post-injury assessments and to achieve the primary and secondary endpoints (15). The assessment time-points for the study (Table 3) include: pre-season baseline, time of injury (optional, 24–48 h following injury, daily symptom and activity tracking through 7 days post-return to play, athlete satisfaction at 7 days post-return to play, and 1-month following full return to play. Each of the assessment timepoints are collected at the approximate windows, i.e., within 5 days, due to the nature of athletic schedules. Study measures are administered by trained site personnel and clinicians. Assessments take place at site medical and training facilities. Below are brief descriptions of all study measures.

**Table 3 T3:** Assessment schedule.

	**Demographics**	**Personal and family history**	**SCAT symptom checklist**	**QOL**	**BSI-18**	**Neurocognitive assessment**	**SAC**	**BESS**	**NPC**	**Dual-task**	**Start and end fatigue rating**
**Pre-season baseline**	✓	✓	✓	✓	✓	✓	✓	✓	✓	✓	✓
**Time of injury (within 6 h—if possible)**			✓				✓	✓			
**24–48 h post-injury**			✓		✓	✓	✓	✓	✓	✓	✓
**Asymptomatic post-injury**			✓	✓	✓	✓	✓	✓	✓	✓	✓
**1-month post return to play post-injury**			✓	✓	✓	✓	✓	✓	✓	✓	✓
- Symptoms and activity assessed daily from the first assessment point until 7 days post return to play - Concussion Index completed following injury - Recovery Form completed following return to play - *Participant Satisfaction completed at 7-days post return to play*											

*QOL, Quality of Life; BSI-18, Brief Symptom Inventory 18 item; SAC, Standardized Assessment of Concussion; NPC, Near Point of Convergence; SCAT, Sport Concussion Assessment Tool*.

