***Specific Aim 1***
*(evaluation of effectiveness):* For analyses of our primary endpoints, Cox proportional hazards regression models (35) will be used to compare time to return to play and time to asymptomatic between the EGE and MDR groups. The specific outcomes for the Cox models will be time from date of injury to: (1) date of medical clearance for full return to participation and (2) asymptomatic date. The Wei-Lin robust variance estimator will be used to account for the effect of cluster-randomization by site (36).

For our secondary endpoints (clinical and quality of life measures), recovery trajectories will be examined by use of General Linear Mixed regression models and non-parametric smoothers. Random effects will be utilized to account for the effect of clustering by site and the effect of repeated observations over time within an individual participant. The time axis to be modeled in both sets of analyses is time from initiation of the treatment (defined as stable symptoms for 24 h), and time will be treated as a continuous variable in all analyses.

We will also assess potential predictors of attrition (e.g., gender, race, socioeconomic status). If no predictable patterns are observed for missing data (i.e., missingness occurs at random), no imputations will be conducted. Inverse probability of attrition weights based on the factors influencing attrition will be used to account for potential selection bias due to attrition. We will assess the differences between the EGE and MDR group participants (those with SCR) at baseline and before starting the treatment protocol.

For sensitivity analyses of primary and secondary, we will conduct intent-to-treat analysis (prescribed treatment), per-protocol analysis (adhered treatment) and use inverse probability weighting to determine potential outcomes had everyone adhered to their prescribed treatments.

To test the effectiveness of randomization, we will compare key variables at baseline and immediately post-injury (24-48 h timepoint) to determine differences between arms. These variables at a minimum will include: age, gender, previous history of concussion, contact/collision sport, baseline symptom severity score, 24–48 h symptom severity score. Should any differences be observed these factors will be controlled for in the models. Additionally, 24–48 h symptom severity will be considered in all analyses.

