### Changing Landscape of SRC Management

Implementing a multiyear pragmatic clinical trial involves understanding the rapidly changing landscape of SRC management. With a rapidly growing evidence base and new treatment and management strategies emerging, it is important to provide a protocol to capture any of these adaptations that may occur in clinical care across the trial. Our trial does not prohibit additional care and clinical decisions outside of the study protocol due to these potential changes. As such, we capture all treatments and activities outside of the study protocol to be able to control and assess how these factors may influence our study outcomes. Additionally, as the study began, the 5th International Consensus Statement on Concussion in Sport (16) had not yet been released. However, we felt symptom limited activity during Stage 1 was often clinically practiced vs. no activity. As such, this has been our protocol from the beginning of the study.

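### The post-injury activity log is given a covariate role, and neither it, outside care nor a late severity score is kept out of the effectiveness models

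*Protocol article*

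**What the plan says.** Four parts of the protocol article bear on this.

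- **Activity log** (Study Arms and Treatment Protocols, text after Figure 1): every participant with a concussion fills in a daily record of physical and mental activity, beginning 24–48 h after injury and ending a week after play resumes. Its role is then given: "The activity log information serves as the primary compliance measure, as well as measures of activity that may affect recovery (covariates". The same section describes the contrast between arms: "Overall, the difference between study arms is the inclusion of early, active rehabilitation".
- **Outside care** (Changing Landscape of SRC Management). The stated purpose concerns the influence of such care on outcomes: "we capture all treatments and activities outside of the study protocol to be able to control and assess". Clinical Variability of SRC repeats the intent. Neither place names a model.
- **Severity at 24–48 h** (Planned Data Analysis, Specific Aim 1): this "symptom severity will be considered in all analyses". It is also among the variables compared between arms and controlled for if a difference is seen.
- **Timing.** Study Outcomes and Assessments: "Each of the assessment timepoints are collected at the approximate windows, i.e., within 5 days". Table 2 allows a first MDR session from 24–48 h after injury, with entry judged against an initial score that may be the 6 h or the 24–48 h one.

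Specific Aim 1 specifies Cox models that compare the arms. Its minimum list of variables covers age, gender, concussion history, contact or collision sport, baseline severity and 24–48 h severity. Per-protocol and inverse-probability-weighted adherence analyses are planned as sensitivity analyses.

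**The concern.** The primary question is what assignment to MDR does to time to asymptomatic and time to clearance. A covariate is safe for that question if treatment cannot have altered it. Three candidates fail that test or may fail it.

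Activity after injury is close to what MDR is meant to change, and an athlete who is recovering also does more. Adjusting for it can remove part of the effect, or create an apparent effect where there is none. A summary over the whole log would also use days after the event being modelled.

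Outside care is chosen after allocation, by site clinicians who know the arm, partly because an athlete needs more treatment. It can reflect slow recovery as well as influence it.

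The 24–48 h severity score is prognostic and worth using, but only while it describes the athlete before treatment. If some scores follow MDR sessions, part of the effect is already in the covariate. The rule of controlling for variables that differ between arms would then tend to bring the score in precisely because treatment had moved it.

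**Working it through.** **1. Is the log a post-treatment variable?** It starts 24–48 h after injury, the earliest MDR start, and ends 7 days after return to play. It therefore covers the treatment period and runs past both primary events. The text calls it a covariate and names no analysis to which that role is confined.

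**2. Can the 24–48 h score follow treatment?**
- If the 24–48 h score is the initial one, 24 h of stability counted from it puts MDR entry later. The order is safe.
- If the 6 h score is the initial one, stability can be met at 6 + 24 = 30 h. A score taken on time at, say, 40 h could follow a first session.
- With the window, a score may come as late as day 5 (window counted from injury) or day 2 + 5 = 7 (counted from the nominal time). At the planned four sessions a week from 30 h, the number of sessions before the score could reach (120 − 30)/24 × 4/7 = 2.1, or (168 − 30)/24 × 4/7 = 3.3.

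This shows what is possible. The article gives no figure for how often it happens.

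**3. The plan's power figure.** Inputs: 100 per arm, ratio 4.5/7 = 0.64, stated power 83% (Sample size; Table 4), attrition 10–15% (Participants and Eligibility Criteria). Two-sided 5% is assumed, since no alpha is stated. As a hazard ratio for the recovery event the ratio is inverted: 7/4.5 = 1.56, with log 0.442. The inversion does not affect power.

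Power = Φ(0.442 × √(events/4) − 1.96)

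At 12.5% attrition, events = 200 × 0.875 = 175, giving Φ(2.92 − 1.96) = 83%. Attrition of 10% gives 84% and 15% gives 82%. The stated figure is reproduced.

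**4. If part of the effect were adjusted away** (assumed shares, 175 events):

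| Share of log HR removed | HR left | Power |
|---|---|---|
| 0 | 1.56 | 83% |
| 25% | exp(0.442 × 0.75) = 1.39 | Φ(2.19 − 1.96) = 59% |
| 50% | exp(0.442 × 0.50) = 1.25 | Φ(1.46 − 1.96) = 31% |

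**5. Simulated Cox models** (200 per arm, 150 replicates per scenario, EGE median 7 days, activity raised 0.8 SD by MDR; all assumed).
- *True effect partly through activity.* With 25, 50, 75 and 100% of the effect passing through activity, the adjusted HR is 1.40, 1.24, 1.12 and 1.01. Without adjustment it stays at 1.56, 1.52, 1.48 and 1.45.
- *No true effect.* MDR raises activity, activity does nothing, and latent recovery (log HR 0.5 per SD) drives both activity and outcome. With correlations of 0.3 and 0.5 between recovery and activity, the unadjusted HR is 0.99 and 1.00; the adjusted HR is 0.89 and 0.84, a false signal against MDR.

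The first scenario pulls the estimate towards no effect. The second pulls it away.

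**The case against.** Specific Aim 1 is the only place that specifies models, and its list contains neither activity nor outside care. Its adherence analyses need activity data, so the covariate label may have been meant for them. The outside-care statements sit in the Discussion and describe what the data would allow. The full covariate set is ordinarily left to the SAP. This stands to the extent that a reader might infer that the plan already adjusts its Cox models for activity and outside care; the article does not say that. It does not remove the point, because the label is stated without restriction, the model list is only a minimum, and the section on care outside the protocol expresses an intent to control.

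The severity score has a good defence. Specific Aim 1 treats that timepoint as immediately post-injury and intends a comparison before treatment starts, and the 6 h assessment is optional, so the 24–48 h score will often be the initial one. It would be wrong to call it a bad covariate. What remains is that no rule secures the order.

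The daily log records general mental and physical activity in both arms under shared guidance, while MDR sessions of about 20 minutes have separate logs. How much of any effect the log would carry is therefore unknown.

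Two further inferences are tempting and unsupported. One is that the bias must run towards no effect; the null simulation shows otherwise. The other is that recovery is planned at 4 to 7 days, so that late scores would follow recovery. Those day counts are only read off the ratio labels in Table 4, and no text states them.

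**Conclusion.** The point holds in a limited form. The article gives a post-allocation activity measure a covariate role, states an intent to control for outside care, and does not ensure that the severity score precedes treatment. Using the first two in the effectiveness models would bias the estimated effect of assignment. The severity score is a problem only where it was taken after treatment began.

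Neither direction nor size can be fixed from the document. The hazard ratios and the fall in power from 83% to 59% or 31% rest on assumed shares, an assumed two-sided 5% level and about 175 events. The simulations rest on assumed links between activity, recovery and arm. All of these illustrate what could happen and do not estimate what will.

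**What to change.** In Study Arms and Treatment Protocols and in Planned Data Analysis, state that the primary and secondary effectiveness models adjust only for (a) pre-injury variables and (b) post-injury symptom severity measured before any MDR session, or before the equivalent pre-treatment time in the EGE arm. Define that time by a rule applied alike in both arms; Specific Aim 1 already equates treatment initiation with 24 h of stable symptoms. Where the 24–48 h score was taken later, use an earlier recorded post-injury score if one exists; otherwise treat the score as missing.

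State also that activity logs and outside care are used only in the planned per-protocol and inverse-probability-weighted adherence analyses, or in mediation analyses labelled exploratory.

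This changes wording and adds no data collection. The downside is small: the time-of-injury assessment is optional, so some participants will have no earlier score, and substituted scores will come from somewhat different times after injury.
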